***2. Data Collection:***

The research will include assessing inclusion and exclusion criteria from clinical data in the EPIC/PennChart EMR that has been collected during regular clinical care prior to the study initiation. This data will determine whether the patient is eligible for the study. Data Science will collect this data to identify and generate lists of eligible study participants. Data Science will again collect clinical data from the EPIC/PennChart EMR to assess the primary and secondary outcomes at the end of the 6 month study period for participants in both the usual care and intervention arms. This data will be combined with home blood pressure readings collected by Way to Health to assess the primary and secondary outcomes.

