**STUDY DESIGN:**

Pragmatic, non-blinded, randomized controlled trial.

Randomization and enrollment:

- Randomization will be at the patient level (stratified/balanced randomization by PCP)
- Enrollment will take place over short time period based off of lists of eligible patients pulled from the EMR
- Lists of eligible patients sent to PCPs with opportunity to opt patients out. Patients will be contacted via text followed by phone call to introduce them to the program.

We expect recruitment to take approximately 1 month to reach a target sample size of 300. The program itself will be 6 months from the date of randomization. Total study duration should be approximately 7 months. Data analyses will take an additional 3 months.

The control group will receive usual care as determined by PCP (control arm will not receive BP cuffs).The Intervention Group will receive the BP cuff and weekly SMS messages asking for the BP reading. The methods section below will outline the details for both groups.

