**METHODS:**

***1. Study Instruments:***

The study instrument comprises of a 6-month study visit to measure blood pressure at the conclusion of the study period and the data that is collected by Way to Health.

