## *2. Group Modifications:*

Patients in the usual care arm will not be contacted by study staff at the start of the pilot, they will not receive a blood pressure cuff, and they will not receive any text messaging or any component of the program. They will eventually be contacted by study staff to schedule the 6 month BP check. Patients assigned to intervention arm will a text message notifying them of enrollment, be mailed a BP cuff and receive a recruitment phone call if nonresponsive to text. If the patient does not opt out, the research coordinator will mail a blood pressure cuff and proper measurement instructions and start their remote monitoring program in the Way to Health platform. Usual care for hypertension is as needed determined by the clinical expertise of the primary care provider and can include regular follow-up visits (in person or virtual), home blood pressure readings, titration of medications during visits or via telephone, referral to specialty care (e.g., Nephrology or Cardiology), blood tests or imaging studies.  Both arms will continue to receive usual care as directed by PCP. Therefore, there are no risks related to foregoing usual care in the intervention arm or in usual care.

*3. Method for Assigning Subjects to Groups:*

Once participants are eligible to begin the study, they will be randomly assigned to the remote monitoring program or usual care. Allocation will be 1:1. The randomization will be at the patient level and stratified by PCP.

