***5. Statistical Analysis:***

**STATISTICAL CONSIDERATIONS**

**Statistical Hypotheses**

- Primary Efficacy Endpoint(s):
  - Hypothesis: The mean decrease in systolic blood pressure from baseline to the 6 month study visit will be 5 mmHg greater in the intervention group relative to the control arm.
- Secondary Efficacy Endpoint(s):
  - Hypothesis 1: Systolic blood pressure will be 5 mmHg lower in the intervention group relative to the control arm at 3 months post randomization, measured pragmatically.
  - Hypotheses 2: Diastolic blood pressure will be 5 mmHg lower in the intervention group relative to the control arm at 3 months (measured pragmatically) and 6 months (study visit) post randomization.
  - Hypothesis 3: The proportion of patients having achieved blood pressure control (as defined by a BP < 140/90) will increase by 10% in the intervention group relative to the control group.

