## *Data Analysis*

## The baseline is the mean of last two BP. The final BP is the one taken at the six month visit.

**RISK/BENEFIT ASSESSMENT:**

***1. Risks:***

We consider this study minimal risk. The primary risk would be from a breach of confidentiality involving medical record reviews and monitoring of hypertension medication and blood pressure measurement adherence with text messaging which will be maintained on the Way to Health platform. This risk has been mitigated by extensive privacy protection protocols, a highly secure data storage system, and a plan to remove identifiers from the data wherever possible. In addition, all personnel will be held to high standards of upholding confidentiality and safeguarding patient privacy

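### The protocol contradicts itself on whether home readings, which only the intervention arm supplies, count towards the outcomes; the 3-month endpoints are the most exposed

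*Protocol*

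**What the plan says.** Two sections bring home readings into outcome assessment. Data Collection (under Study Procedures) has clinical data extracted from the medical record "for participants in both the usual care and intervention arms", and then adds: "This data will be combined with home blood pressure readings collected by Way to Health to assess the primary and secondary outcomes". The sentence names the primary outcome and carries no limit. Study Instruments likewise lists "a 6-month study visit to measure blood pressure at the conclusion of the study period and the data that is collected by Way to Health".

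Those readings come from one arm. Study Design says the "control arm will not receive BP cuffs", and Group Modifications says of usual-care patients that "they will not receive any text messaging or any component of the program".

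Other sections define the 6-month outcome differently. Statistical Hypotheses, Sample Size Determination and Analysis of the Primary Efficacy Endpoint(s) all refer to the 6-month study visit, and Data Analysis states: "The final BP is the one taken at the six month visit". Administration of Surveys and/or Process lists that in-person visit for both arms. The 6-month diastolic endpoint is also tied to it.

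At 3 months no visit is scheduled. The systolic endpoint is set "at 3 months post randomization, measured pragmatically", the 3-month diastolic endpoint is described in the same way, and no source is named for either.

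**The concern.** A blood pressure texted from home and one taken in a clinic are different measurements. If the first kind can enter the outcome in one arm only, any systematic difference between them is added to the treatment contrast. So is any tendency to reply to some prompts and not others. Randomisation does not protect against this, because the difference arises after allocation and by arm.

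At 6 months the route is practical. The sample-size section needs about 200 of 300 randomised patients, so it allows for one third lost, while the primary analysis is to follow intention to treat. Someone applying the Data Collection sentence could fill a missed visit with a home reading, and could do so only in the intervention arm.

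At 3 months nothing in the document rules this out. The only statement on how outcome data are assembled is the combining sentence, which permits texted readings in one arm against medical-record readings in the other. Change scores would then also mix sources within the intervention arm, because baseline is the mean of the last two readings, taken before any program reading exists.

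The trial is not blinded, so an unresolved choice of source could be settled after arm-level data have been seen.

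**Working it through.** **1. The passages side by side**

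| Outcome | Source under Data Collection / Study Instruments | Source under the endpoint definitions |
|---|---|---|
| 6-month systolic (primary) | Medical record plus home readings | Study visit, both arms |
| 6-month diastolic | Medical record plus home readings | Study visit, both arms |
| 6-month control (<140/90) | Medical record plus home readings | Final BP is the visit value (Data Analysis) |
| 3-month systolic and diastolic | Medical record plus home readings | Pragmatic; source not named |

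The first three rows are a contradiction. The last row is an open choice that the combining sentence allows to differ by arm.

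**2. The plan's own figure**

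Inputs from Sample Size Determination: difference 7 mmHg, SD 17, power 80%, alpha 0.05; two-sided by the General Approach.

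n per arm = 2 × (1.960 + 0.842)² × 17² / 7² = 93 after rounding up, or 186 in total. The stated figure of about 200 is somewhat larger (power 82.9% at 100 per arm). The point does not depend on this. The figure is used only to set a standard error:

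SE = 17 × √(2/100) = 2.40 mmHg.

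**3. Size of the bias (illustration)**

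Bias = f × b, where f is the share of intervention-arm outcome values taken from home and b is the amount by which home readings run below clinic readings. The documents give neither, so both are assumptions. With no true effect,

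type I error = Φ(−1.96 + bias/SE) + Φ(−1.96 − bias/SE).

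| f (assumed) | b, mmHg (assumed) | Bias, mmHg | Type I error |
|---|---|---|---|
| 0 (visit value only) | any | 0 | 0.050 |
| 0.25 | 2 | 0.5 | 0.055 |
| 0.50 | 2 | 1.0 | 0.070 |
| 0.50 | 5 | 2.5 | 0.18 |
| 0.80 | 5 | 4.0 | 0.384 |

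The hypothesised effect is 5 mmHg.

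**4. The missed-visit case**

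Suppose one third of each arm misses the visit and home readings fill the gap in the intervention arm only, so that 150 are compared with 100. Then SE = 17 × √(1/150 + 1/100) = 2.19. With f = 1/3 and b of 2 to 5 mmHg, the bias is 0.7 to 1.7 mmHg and the type I error 0.061 to 0.118.

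**The case against.** The strongest reply is that the primary endpoint is already fixed. Four sections define it by the 6-month visit, the visit is in person for both arms, and attendance is compensated. The combining sentence is a general remark on data collection and contains no rule for replacing a visit value with a home value. A reader might infer from it that the primary result will be confounded. The document does not support that: under the endpoint definitions the home share is zero and so is the bias. This part of the objection stands, and the 6-month problem is a contradiction with a conditional consequence.

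A reader might also conclude that the 3-month endpoints are unusable. That goes too far. The protocol names no source for them, and rules on source and window are often left to an analysis plan, which is not shown. What remains is that the protocol's one stated rule permits unequal sources. Nor are the home readings simply self-selected: prompts go out weekly at a set time, although patients decide whether to answer.

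The illustration is also limited. It uses planning values for 6-month systolic pressure. The document gives no 3-month sample size or SD, and no diastolic SD, so the figures do not measure the most exposed endpoints.

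Usual care may include home readings in either arm. These are not Way to Health data, so they do not restore balance.

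**Conclusion.** The point holds as a contradiction to be reconciled, together with an unprotected choice of source at 3 months. It is more than missing detail, because the protocol states affirmatively that readings available in one arm will be used for the primary and secondary outcomes.

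If the visit definition governs, the 6-month endpoints carry no such bias and type I error stays at 5%. If the combining sentence is followed, a false benefit of 1.0 mmHg raises it to about 7%, and one of 4.0 mmHg to about 38%. These figures rest on assumed home shares (50% and 80%), assumed offsets (2 and 5 mmHg), home readings running lower than clinic readings, SD 17 and 100 per arm. If home readings ran higher, the same mechanism would hide a benefit. The control endpoint would be exposed to the same shift. Whether the combining sentence is a drafting slip cannot be settled from the document.

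**What to change.** - **Data Collection and Study Instruments:** remove the use of Way to Health readings for outcomes. State that all 6-month outcomes, including blood pressure control, use only the study-visit value in both arms, and that a home reading never replaces a missed visit.
- **3-month outcomes:** name one source for both arms, namely clinic-measured values from the medical record within one fixed window, with patient-reported values excluded.
- **Way to Health readings:** keep them for describing engagement within the intervention arm, or for a clearly labelled supportive analysis.

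The sample size is unaffected and the wording change is a few sentences. The real cost falls at 3 months. There will be fewer values, and they will come from patients who happened to attend. Remote monitoring could itself change who attends, so a common source does not remove selection. The number and proportion of patients with a 3-month value should be reported by arm, and those results interpreted cautiously.

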***5. Statistical Analysis:***

**STATISTICAL CONSIDERATIONS**

**Statistical Hypotheses**

- Primary Efficacy Endpoint(s):
  - Hypothesis: The mean decrease in systolic blood pressure from baseline to the 6 month study visit will be 5 mmHg greater in the intervention group relative to the control arm.
- Secondary Efficacy Endpoint(s):
  - Hypothesis 1: Systolic blood pressure will be 5 mmHg lower in the intervention group relative to the control arm at 3 months post randomization, measured pragmatically.
  - Hypotheses 2: Diastolic blood pressure will be 5 mmHg lower in the intervention group relative to the control arm at 3 months (measured pragmatically) and 6 months (study visit) post randomization.
  - Hypothesis 3: The proportion of patients having achieved blood pressure control (as defined by a BP < 140/90) will increase by 10% in the intervention group relative to the control group.

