## *4. Administration of Surveys and/or Process:*

## Control Group

## 6 month in person clinic visit

## Intervention Group

## Communication via W2H

## 6 month in person clinic visit

##

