
## STUDY PROCEDURES:

***1. Detailed Description:***

For the intervention arm, after the PCP has had the opportunity to opt out any patients they deem inappropriate, the research team will create encounters in Penn Chart and upload the list to Way To Health including the MRN and CSN. Way To Health will start enrollment for intervention patients and send introduction via text messages. The patient outreach text can be found in patient outreach document.

On a rolling basis as patients’ complete orientation, the research team will mail BP cuffs. For patients who do not complete the text message orientation, the research team will call the patients up to two times. The first phone call will be three business days after the initial outreach and the second call will be seven business days after the initial outreach. If there is no response, the patient will be deemed as “do not contact” and the research team will change their status to inactive in Way To Health.

For patients who get started in the program Way To Health will change their status to “active”. The BP reminder will begin when patients text in “READY”. The notifications will be sent to the research team when the patient starts, and the research team will update Penn Chart with documentation. If the patient does not text back “READY” then the research team will call the intervention patient up to two times, the first being 10 days after mailing and the second being 14 days after mailing

For enrollment documentation when the patient texts “READY” or confirms readiness by phone call a telephone encounter will be created to document patient enrollment. The PCP will then be able to continue to manage their patient as they normally would. Any encounters resulting from interactions via the remote monitoring program will be routed to the PCP inbox. The research team will notify the PCP of any medication changes. If the patient opts out after starting, a telephone encounter will be created, and the research team will be notified and will notify the PCP.

The BP request messaging is in the Patient and Provider materials document that is attached and will be sent weekly on the specified day and time that the patient indicated in the enrollment survey.

The BP Logic categorization is in the below table. Further information on the logic and messaging can be found in the attached Patient and Provider materials document.
[figure not shown]

[figure not shown]

[figure not shown]

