***Analysis of the Secondary Endpoint(s)***

Secondary endpoints will include the change in systolic blood pressure at 3 months post randomization; change in diastolic blood pressure measured at 3 months and 6 months; and blood pressure control (<140/90) at 6 months. The statistical approach for continuous measures will be similar to that described above. For the binary outcome of blood pressure control, crude differences will be assessed with a chi-squared test, and we will use a logistic regression model with adjustment for covariates as described above.

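### The 3-month blood pressure hypotheses have no common 3-month measurement, so the arms can differ in reading source and in who has a reading

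*Protocol*

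**What the plan says.** Under Statistical Hypotheses, secondary Hypothesis 1 sets systolic pressure 5 mmHg lower in the intervention arm than in the control arm "at 3 months post randomization, measured pragmatically". Hypothesis 2 sets the same 5 mmHg for diastolic pressure "at 3 months (measured pragmatically) and 6 months (study visit) post randomization". The protocol does not say what pragmatic measurement means: it gives no time window, no rule for choosing among readings and no source.

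Analysis of the Secondary Endpoint(s) states: "The statistical approach for continuous measures will be similar to that described above". That refers back to the primary analysis, a t-test and a linear regression. General Approach applies a two-sided 0.05 cutoff.

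The scheduled measurements are elsewhere. Study Instruments: "The study instrument comprises of a 6-month study visit to measure blood pressure at the conclusion of the study period". The arm-by-arm list under Administration of Surveys and/or Process gives each arm a "6 month in person clinic visit" and adds only platform messaging for the intervention arm. Compensation pays for the 6-month measurement alone.

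On contact, Group Modifications says: "Patients in the usual care arm will not be contacted by study staff at the start of the pilot". Controls get no cuff and no texts, and are contacted later to book the 6-month check. Usual care has no fixed schedule. Study Design gives the intervention arm a cuff and weekly requests for a reading. Data Collection combines the platform's home readings with record data for the primary and secondary outcomes. Detailed Description adds: "Any encounters resulting from interactions via the remote monitoring program will be routed to the PCP inbox".

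**The concern.** A hypothesis test between randomised arms needs an outcome obtained in the same way in both. At 6 months the study visit supplies that. At 3 months nothing does. The control value comes from whatever routine care happened to record, while the intervention value may come from a weekly home channel that exists in that arm only.

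Two differences between the arms follow. The first is source: a home reading in one arm may be set against an office reading in the other. The second is ascertainment: the patients with a value are a subset formed after randomisation, and the way it forms can differ by arm. A t-test on available values treats these subsets as the randomised groups. A real 3-month benefit could be hidden, or an apparent one produced, and the reported p-value would not show which.

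**Working it through.** **1. Where a 3-month value can come from.**

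| | Control | Intervention |
|---|---|---|
| Scheduled 3-month study measurement | none | none |
| Study cuff | no | yes |
| Study home readings | none | requested weekly |
| Office reading near 3 months | only if routine care records one | only if routine care, or care prompted by the program, records one |
| Home readings used for outcomes | none collected by the study | yes, under Data Collection |

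The differences in source and in opportunity to have a value are therefore in the text. How often each kind of reading occurs is not.

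**2. The plan's own sample-size figure.** It concerns 6 months. With a difference of 7, SD 17, 80% power and two-sided 0.05:

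n per arm = 2 × (1.960 + 0.842)² × 17² / 7² = 92.6, so 93 per arm and 186 in all (188 with the t distribution).

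The protocol says about 200, and 100 per arm gives 82.9% power. That is cautious rounding, and nothing here depends on it. No 3-month sample size or expected share with a reading is given.

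**3. Power for 5 mmHg at 3 months (SD 17, share with a reading assumed equal in both arms).** The standard error is 17 × √(2/m), with m patients per arm. With all 150 per arm it is 1.96 and power is 72%. With half (m = 75) it is 2.78 and power is 44%. With 30% (m = 45) it is 3.58 and power is 29%.

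**4. How far selective observation can move the estimate.** SD 17 is from Sample Size Determination; everything else is assumed: true 3-month means of 140 (control) and 135 (intervention), a true difference of −5, and office-reading probability p₀ at or below 140 and p₁ above it. The mean among those seen is

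μ + 17 × φ(z) × (p₁ − p₀) / [p₀Φ(z) + p₁(1 − Φ(z))], with z = (140 − μ)/17.

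Intervention: z = 0.294, Φ = 0.616, φ = 0.382, so 17φ = 6.50. Control: z = 0, Φ = 0.5, φ = 0.399, so 17φ = 6.78.

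| p₀ / p₁ | Shift, intervention | Difference if only intervention selects | Shift, control | Difference if both select alike |
|---|---|---|---|---|
| 0.4 / 0.5 | 6.50 × 0.1/0.438 = +1.5 | −3.5 | +1.5 | −5.0 |
| 0.4 / 0.6 | 6.50 × 0.2/0.477 = +2.7 | −2.3 | +2.7 | −5.0 |
| 0.3 / 0.6 | 6.50 × 0.3/0.415 = +4.7 | −0.3 | +4.5 | −4.8 |

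Partial asymmetry (0.4/0.6 intervention, 0.4/0.5 control) gives −3.8. Selection the other way in the intervention arm only gives −6.4 (0.5/0.4) and −7.5 (0.6/0.4).

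**5. Whether a model repairs it.** I simulated the three one-sided scenarios with baseline and 6-month pressure known for everyone and an assumed correlation of 0.5 between time points. A model valid under missing at random gives about −4.0, −3.2 and −1.9 against −5. That is closer than −3.5, −2.3 and −0.3, but still biased, because being seen depends on the 3-month value itself.

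The home-versus-office difference is left unquantified, since the documents give no figure for it.

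**The case against.** The strongest reply is that the trial is openly pragmatic, these are secondary endpoints, and the statistical analysis plan, which is not shown, may define the window, the choice of reading and the handling of missing values. That stands for those details. It does not answer the main point: no analysis plan can create a shared 3-month measurement for controls.

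A reader might go further and infer that the program demonstrably changes who is seen in clinic. The documents do not show this. Detailed Description routes encounters to the PCP inbox, but the ones it spells out are chart and telephone entries, not visits with an office reading. The figures with the blood pressure logic are not shown. BP-dependent visits in the intervention arm are a possibility only.

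Usual care is as needed, so control visits may also depend on pressure. If both arms select alike, the bias nearly vanishes. The one-sided column in the working is an illustration of what could happen, not an estimate.

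A reader might also take the onboarding delay as an error, because the same 5 mmHg systolic effect is hypothesised at 3 and 6 months. It is not one: an intention-to-treat effect counted from randomisation includes start-up time, and equal effects at two times are not contradictory.

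**Conclusion.** The concern holds for the systolic comparison in Hypothesis 1 and for the 3-month half of Hypothesis 2. As written, both are tested like the primary endpoint although the arms share no 3-month measurement and home readings enter from one arm only. It would be too strong to say that two whole secondary hypotheses cannot be answered: 6-month diastolic pressure and 6-month blood pressure control are separate endpoints and are not in question here, nor is the primary.

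The size and direction of the bias are unknown. Under the assumed means and visit probabilities, with SD 17 from the protocol, it ranges from near zero (both arms select alike) to between 1.5 and 4.7 mmHg towards no effect (only the intervention arm selects, with higher pressures seen more often). It reverses sign if lower pressures are seen more often. Any source difference between home and office readings would come on top. This should be changed before the 3-month results are analysed, but it does not threaten the trial's main conclusion.

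**What to change.** - **Statistical Hypotheses and Analysis of the Secondary Endpoint(s):** label the 3-month systolic and diastolic comparisons exploratory. Keep 6-month diastolic pressure and 6-month blood pressure control as the tested secondary endpoints.
- **Data Collection:** state that home readings are not used for between-arm blood pressure comparisons. For 3 months, use only office readings from the health record in both arms, within one fixed window around day 90.
- **Reporting:** give the share of randomised patients with a 3-month reading, by arm.
- **Analysis:** estimate the 3-month difference in a repeated-measures model that includes baseline and 6-month pressure, instead of a t-test on those seen. State that it relies on missing at random, and that it reduces selection bias but may not remove it.

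The cost is wording in three sections and one added model, with no new visits. The 3-month result loses its status as a tested hypothesis, and fewer intervention patients contribute a 3-month value once home readings are set aside. Restricting to office readings removes the source difference but not the selection, which is why the exploratory label is the main change.
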